A number of international and national recommendations for the management of PsA and corresponding treatment algorithms have been published in the past few years in both rheumatology and dermatology (28-31, 34, 35). Ideally, management of PsA should address joints and skin as well as extra-articular manifestations and comorbidities (34, 35). It has been demonstrated that PsA patients receiving a multidisciplinary care, involving both rheumatologists and dermatologists in a US clinic, were more likely to receive systemic medication (25% vs 15%) and be treated with a biologic agent (37% vs 16%) than in prior unidisciplinary care (36).

While consensus is evident among the recommendations on the main treatment principles, the extent to which they are followed by practicing physicians is unknown. In reality it appears that many patients with PsA are not diagnosed, or are undertreated or not treated systematically (34, 37). A recent large population based multinational survey conducted in North America and Europe revealed that approximately 15% of patients with PsA had not seen a health care provider in the past year, and almost 60% were not being treated for their joint disease (38).

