## **6.2. Study Duration**

This is a cross-sectional, observational study. The inclusion period will be approximately 16-18months.

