## 8. Data Analysis Plan

### 8.1. Endpoints

#### Primary Endpoints

- Time from inflammatory musculoskeletal symptom onset to PsA diagnosis
- Time from PsA diagnosis to first csDMARD
- Time from PsA diagnosis to first bDMARD
- Time from first csDMARD to first bDMARD

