### 8.2. Plan for Statistical Analysis

Only patients with a confirmed diagnosis of PsA will be eligible for statistical analysis. The exact definition of the analysis populations will be detailed in a separate statistical analysis plan.

Collected data will be summarized by descriptive statistics. Quantitative variables will be reported as absolute N, mean, standard deviation, median, 1st and 3rd quartiles and minimum and maximum. Qualitative variables will be reported as absolute and relative frequency distributions.

Research outcomes of primary and secondary interest will be analyzed using descriptive statistics overall and in subgroups defined by explanatory variables (disease severity perception by patients and physicians and clinical specialty). Effects will be estimated depending on the scale of the endpoint by use of mean differences or ORs with respective 95% confidence interval. The effect estimates will be calculated from simple regression

Confidential Information

No use or disclosure outside AbbVie is permitted without prior written authorization from AbbVie

models run separately for each of the explanatory variables and thereafter in multiple regression models with variable selection to identify and assess important explanatory variables. Depending on the scale of the dependent variable, linear or logistic models will be used.

PsA clinical manifestation and disease burden will be analyzed using descriptive statistics. Regression analyses will be done as described above, using time from symptom onset to PsA diagnosis, time from PsA diagnosis to first csDMARD, first bDMARD and from first csDMARD to first bDMAD as explanatory variables.

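### Three of the four primary times are right-censored at the study visit, but section 8.2 provides only mean differences or odds ratios from linear or logistic models

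*Protocol*

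**What the plan says.** Section 8.1 of the protocol lists four primary endpoints: "Time from inflammatory musculoskeletal symptom onset to PsA diagnosis", "Time from PsA diagnosis to first csDMARD", "Time from PsA diagnosis to first bDMARD" and "Time from first csDMARD to first bDMARD". Under section 5 the primary objective is to relate these times to the clinical specialty setting.

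Section 6.2 states: "This is a cross-sectional, observational study". Disease and treatment history come from the charts around a routine visit (section 6.1), so nothing after the study visits is known.

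On analysis, section 8.2 says: "Effects will be estimated depending on the scale of the endpoint by use of mean differences or ORs with respective 95% confidence interval". It adds: "Depending on the scale of the dependent variable, linear or logistic models will be used". Patients qualify for analysis by having confirmed PsA; having started a DMARD is not required. Section 8.2 leaves the definition of the analysis populations to the SAP, but it states the effect measures and model types itself.

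Section 8.3 sizes the study on two-sample t-tests of means: 400 vs 400 at an effect size of 0.229 and 400 vs 200 at 0.281, each with 90% power. The only loss allowed for is non-confirmed diagnosis. Censoring, time-to-event methods and patients without a DMARD start are not mentioned anywhere.

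**The concern.** A confirmed patient with no csDMARD or bDMARD start by the visit has no completed value for the corresponding time; all that is known is that it exceeds the time from diagnosis to visit. The same holds for a csDMARD starter who has had no bDMARD. The named methods leave three options:

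- A linear model on patients with a start conditions on the outcome and cuts every observed time at that patient's own disease duration.
- A linear model with time to visit entered for the others understates their times.
- A logistic model of started or not keeps everyone, but ignores how long each patient was observed and does not analyse the stated time.

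A setting that starts treatment in few of its patients could then look as quick as one that starts it in most, and settings that differ only in disease duration could appear to differ in speed. Section 8.2 also uses the same three times as explanatory variables for disease activity and burden, where patients without a start again have no value.

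**Working it through.** **1. The plan's own figures.** The effect detectable with 90% power at two-sided 5% is (1.960 + 1.282) × √(1/n₁ + 1/n₂).

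- 400 vs 400: 3.242 × 0.0707 = 0.229.
- 400 vs 200: 3.242 × 0.0866 = 0.281.

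Both stated effect sizes reproduce; exact t-test power is 89.9% and 90.0%. Recruitment also reproduces: 400/0.90 = 445, 400/0.85 = 471 and 200/0.75 = 267 total 1183, which the protocol rounds up to 450 + 480 + 270 = 1200. All of this takes every confirmed patient to have a value.

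**2. Power when only patients with a start contribute a time.** The share with a start is assumed equal in both groups, with 400 per group before loss and an effect size of 0.229.

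| Share with a start | n per group | Power | Detectable effect at 90% |
|---|---|---|---|
| 100% | 400 | 90% | 0.229 |
| 75% | 300 | 80% | 0.265 |
| 50% | 200 | 63% | 0.324 |
| 25% | 100 | 36% | 0.458 |

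The 400 vs 200 comparison at 0.281 gives the same power to within a fraction of a point.

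**3. Bias, illustrated.** Every input here is an assumption; the protocol gives no hazards, treated shares or disease durations. Let time to treatment be exponential with true mean m, and time from diagnosis to visit be independent and exponential with mean f. Then the mean time among treated patients is 1/(1/m + 1/f), and the odds of being treated by the visit are f/m.

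| Case | Setting A (m, f), years | Setting B (m, f), years | Treated-only means A, B | Difference B − A | True difference |
|---|---|---|---|---|---|
| Attenuated | 5, 5 | 10, 5 | 2.50, 3.33 | 0.83 | 5 |
| Reversed | 5, 5 | 10, 2.5 | 2.50, 2.00 | −0.50 | 5 |
| Spurious | 10, 8 | 10, 4 | 4.44, 2.86 | −1.6 | 0 |

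For example, in the first row B is 1/(0.1 + 0.2) = 3.33.

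The other two options fail in the same model. Entering time to visit for untreated patients averages the smaller of the two times, whose mean is also 1/(1/m + 1/f), so the same differences result. For the logistic model, the third row gives odds of 8/10 = 0.8 and 4/10 = 0.4, an odds ratio of 2.0 although the two settings start treatment at the same rate.

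**4. A second censoring pattern.** Constant hazards are kept, but the visit is uniform between 0 and F years after diagnosis. The mean among treated patients is ∫ t·h·e^(−ht)(1 − t/F) dt divided by ∫ h·e^(−ht)(1 − t/F) dt, both over 0 to F.

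- Hazards 0.15 vs 0.075 per year, F = 10 in both: treated-only means 2.59 vs 2.94 years (48% vs 30% treated), a gap of 0.35. The true means are 1/0.15 = 6.7 and 1/0.075 = 13.3 years, a gap of 6.7 (13.33 − 6.67).
- Equal hazards 0.10, F = 15 vs 5: 3.89 vs 1.53 years, a spurious gap.
- Hazard 0.15 with F = 15 vs 0.075 with F = 5: 3.43 vs 1.57 years, so the faster setting looks slower.

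The same three outcomes appear under both patterns.

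**The case against.** The protocol never says that patients without a DMARD start are dropped. It excludes only those without confirmed PsA, and its provision for odds ratios would allow started or not to be modelled with everyone kept. This stands as a limit on wording: exclusion is a consequence of fitting a linear model, not a stated rule. It does not rescue the plan, since the logistic route ignores observation time and does not estimate the listed endpoints.

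Three stronger readings are tempting and are not supported.

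- A reader might conclude that the primary objective as a whole goes unanswered. It does not: symptom onset to diagnosis is complete in principle for every confirmed patient.
- A reader might take the specialty comparison to be biased by a known amount or in a known direction. The protocol does not say that disease duration or treated share differs by specialty, and the reversed and spurious cases rest on assumed differences in observation time.
- A reader might take the survey figure in section 3, "almost 60% were not being treated for their joint disease", as the share with no start here. It describes current treatment in a population survey, whereas this study recruits clinic attenders and asks about first-ever use.

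Section 8.3 calls the study exploratory. That justifies making no multiplicity adjustment and means that no confirmatory claim depends on these models, but it does not remove bias from an estimate. Nor is this simply detail left to the SAP, which was not at hand: the protocol itself states the effect measures and model types.

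**Conclusion.** The point holds for three of the four primary endpoints. The protocol names no method that handles censoring for them, and none of the methods it names can validly use patients without a start. The mechanism follows from the endpoint definitions and the cross-sectional design alone. Its size does not: the illustrations run from a 5-year difference shrinking to 0.83 years, through a spurious 1.6 years, to a reversed sign, all under assumed constant hazards and assumed observation times. The 90% power is correctly calculated, but only for an endpoint observed in every evaluable patient; it falls to 80%, 63% or 36% if 75%, 50% or 25% have a start.

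**What to change.** In section 8.2, for the three DMARD endpoints:

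- Use Kaplan-Meier estimates and Cox or accelerated failure time models by specialty, including all confirmed patients at risk.
- Censor patients without a start at the last study visit at which treatment history is documented, and never before the diagnosis date. This needs care because Table 1 records treatment at the recruiting site, while confirmation of PsA can come at a consulting visit, usually within 12 weeks. A patient whose diagnosis is dated to that later visit contributes no time at risk unless treatment status is also recorded then.
- For csDMARD to bDMARD, take csDMARD starters without a prior bDMARD as the risk set.
- Report separately patients whose DMARD began before the PsA diagnosis, or whose bDMARD came before any csDMARD.
- Give the percentage started at fixed times and the never-started share by specialty.

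Linear models can stay for completely observed outcomes such as the HAQ-DI score.

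In section 8.3, state that 90% power at effect sizes 0.229 and 0.281 applies only to an endpoint observed in every evaluable patient.

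The cost is protocol wording and standard programming, with no change to recruitment. The visit date must be available, which the endpoints as now defined do not require. Results become hazard ratios or time ratios and percentages at fixed times instead of mean differences. The models also assume that, within specialty, time from diagnosis to visit is unrelated to time to treatment; the report should say so.

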## 6. Observational Plan

### 6.1. Study Conduct

This study will be performed in a cross-sectional, observational, multi-country, multi-center format in approximately 15 countries across different geographical regions.

The study population will consist of patients who are 18 years or older, have been diagnosed with suspected or established Psoriatic Arthritis (PsA) and attending a routine clinical visit at the participating clinical sites. Suspected PsA diagnosis is based on clinical judgement of the recruiting physician.

In order to describe the overall PsA population, all specialties providing medical care of PsA patients will be included. The study will be conducted in a convenience sample recruited at rheumatology, dermatology, other specialist and primary care practices. These are providing medical care for 37-38% (rheumatology), 22-28% (dermatology), 7-12% (other specialists) and 28% (primary care practices) of PsA patients, respectively, depending on the country (38). Other specialties may include orthopedists, ophthalmologists, physiatrists and podiatrists according to the standard practice in the respective country (34). For the sake of convenience, other specialist and primary care practices will be referred to as non-rheum/non-derm sites in this research plan.

Patients with a suspected or an established diagnosis of PsA scheduled for routine visit at the recruiting site (dermatologist, rheumatologist or a non-rheum/non-derm site) can be offered the opportunity to participate in the study. Patients will be recruited on a consecutive basis. Patient characteristics, relevant co-morbidities and medical history, disease, diagnostic and treatment data will be documented in the Data Recording Form (DRFs) for data available in the medical charts.

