### 8.3. Sample Size Calculation

The factor that is most likely to influence the PsA management components of interest is clinical specialty. However, there is no scientific basis currently to judge the effect size.

So this will be an exploratory study and objectives are exploratory in nature (non-confirmatory) and no adjustment for multiplicity will be made.

With 400 evaluable patients in rheum and dermatology sites, the study has 90% power to detect a difference in means between the two specialties with a two-sample t-test at a significance level of 5% assuming an effect size of 0.229. With 400 evaluable patients in rheum or dermatology sites and 200 evaluable patients in non-rheum/non-dermatology sites, the study has 90% power to detect a difference in means between rheum vs. non-rheum/non-dermatology or dermatology vs. non-rheum/non-dermatology, respectively, with a two-sample t-test at a significance level of 5% assuming an effect size of 0.281.

The estimated drop-out rates due to non-confirmed PsA diagnosis are 10% in rheum, 15% in dermatology and 25% in non-rheum/non-dermatology sites. Hence, a total number of approximately 1200 patients (450:480:270 in rheum:dermatology:non-dermatology/non-rheum, respectively) has to be recruited in order to achieve 1000 evaluable patients (400:400:200 in rheum:dermatology:non-dermatology/non-rheum, respectively).

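### Section 8.2 takes specialty contrasts from linear models over planned groups of 400:400:200 without allowing for unequal SDs; if the SDs differ, the 95% intervals lose their stated coverage, and robust standard errors would prevent this at almost no cost

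*Protocol*

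**What the plan says.** Section 8.2 of the protocol says that effects will be estimated "by use of mean differences or ORs with respective 95% confidence interval". The explanatory variables are "disease severity perception by patients and physicians and clinical specialty". The estimates come from simple regression "models run separately for each of the explanatory variables and thereafter in multiple regression models with variable selection", and on the model class: "Depending on the scale of the dependent variable, linear or logistic models will be used". No variance estimator is named. The section leaves the exact definition of the analysis populations to a separate SAP, which is not at hand.

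Section 8.3 aims for "1000 evaluable patients (400:400:200 in rheum:dermatology:non-dermatology/non-rheum, respectively"). Rheumatology versus dermatology is sized at 90% power "with a two-sample t-test at a significance level of 5% assuming an effect size of 0.229". For the third group the text reads "With 400 evaluable patients in rheum or dermatology sites and 200 evaluable patients in non-rheum/non-dermatology sites", with 90% power at an effect size of 0.281. No SD is given, and the section says that nothing is known on which to base an effect size.

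On the make-up of the third group, Section 6.1 says that "other specialist and primary care practices will be referred to as non-rheum/non-derm sites in this research plan". Section 6.1.2 lists primary care, orthopedists, ophthalmologists, physiatrists and podiatrists as possible members.

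**The concern.** A linear model with specialty as a three-level factor estimates one residual variance and uses it for every contrast. With groups of equal size, a comparison of two groups is fairly tolerant of unequal SDs. At 400:400:200 that protection is weaker. The pooled variance is dominated by the two large groups, so if the small group is more variable its own error is understated, while the error of the contrast between the large groups is overstated. This does not depend on skewness or on clustering of patients within sites.

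Unequal spread is conceivable here because the smallest group is mixed by design. The specialty contrast is the primary objective, and the intervals are the main inferential output of an exploratory study. They should therefore have the coverage printed beside them.

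**Working it through.** **Inputs.** Group sizes 400, 400 and 200 and the t-test figures come from Section 8.3. The linear model comes from Section 8.2. The ratio r, the SD of the non-rheum/non-derm group divided by the common SD of the other two, is not in the documents. It is assumed, with a main range of 1 to 2 and 0.8 added to show the other direction. The SD of the two large groups is set to 1.

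**The plan's own figures (r = 1).** Detectable difference at 90% power, two-sided 5%: (1.960 + 1.282) × √(1/n₁ + 1/n₂).

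- 400 vs 400: 3.242 × 0.0707 = 0.229.
- 400 vs 200: 3.242 × 0.0866 = 0.281.

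Both stated effect sizes reproduce. By the noncentral t distribution the power is 89.9% and 90.0%.

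**Interval coverage under unequal SDs.**

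- Pooled variance: s² = (399 + 399 + 199r²)/997.
- Model SE for a contrast with the third group: √[s²(1/400 + 1/200)]; true SE: √(1/400 + r²/200).
- Rheumatology vs dermatology: model SE √(s² × 2/400), true SE √(2/400), so their ratio is √s².
- Coverage = 2Φ(1.96 × model SE / true SE) − 1.

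For r = 1.5: s² = (798 + 447.75)/997 = 1.249. Model SE = √(1.249 × 0.0075) = 0.0968 and true SE = √(0.0025 + 0.01125) = 0.1173. The ratio is 0.826 and coverage is 89.4%.

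| r | s² | Model SE / true SE, contrasts with third group | Coverage | Model SE / true SE, rheum vs derm | Coverage |
|---|---|---|---|---|---|
| 0.8 | 0.928 | 1.105 | 97.0% | 0.963 | 94.1% |
| 1 | 1.000 | 1.000 | 95.0% | 1.000 | 95.0% |
| 1.25 | 1.112 | 0.899 | 92.2% | 1.055 | 96.1% |
| 1.5 | 1.249 | 0.826 | 89.4% | 1.118 | 97.2% |
| 2 | 1.599 | 0.730 | 84.8% | 1.264 | 98.7% |

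**Other patterns of spread** (SDs in the order rheumatology : dermatology : third group).

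| SDs | Rheum vs third | Derm vs third | Rheum vs derm |
|---|---|---|---|
| 1 : 1.25 : 1.5 | 92.1% | 90.6% | 96.5% |
| 1 : 1.5 : 1.5 | 94.5% | 91.6% | 95.8% |
| 1 : 1.5 : 1.25 | 96.6% | 93.7% | 94.9% |

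**Simulation check.** Lognormal times, coefficient of variation 1, SD proportional to mean, 10,000 runs. Pooled-variance coverage of the two third-group contrasts is 89.6% and 89.7% at r = 1.5, and 85.1% and 85.2% at r = 2. With separate-variance intervals all three contrasts cover about 94 to 95% for r from 1 to 2.

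**Detectable difference at r = 1.5 with a correct SE.** 3.242 × 0.1173 = 0.38 in rheumatology-SD units, against 0.281 at r = 1.

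**The case against.** The strongest reply is that the protocol fixes the mean model and not the standard error. A robust or Welch-type interval already complies with Section 8.2, and such a detail is commonly left to the SAP, which may contain it. This stands in part: nothing in Section 8.2 has to be undone. But an analyst who follows the text as written would by default fit a single residual variance, and the unequal group sizes are fixed here.

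Four stronger readings are tempting, and the documents do not support them.

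- *The intervals for the third group are too narrow.* No SD is given. With equal SDs there is no error, at r = 0.8 the direction reverses, and with dermatology the most variable the rheumatology versus third group interval is too wide.
- *The third group is the long-delay group, so it must vary more.* Section 4 says that non-rheumatologists and patients find the disease hard to recognise. That covers dermatologists too, and concerns delay to diagnosis only. Groups are defined by recruiting site, and a patient recruited in primary care may have been diagnosed elsewhere.
- *The false-positive rate exceeds 5%.* The coverages above would correspond to 7.8%, 10.6% and 15.2% at r = 1.25, 1.5 and 2, but only if the SDs differ while the means are equal. A larger SD that arises from a longer mean is not available under that null, so only the mixed make-up of the group remains as a reason.
- *The power at 0.281 collapses.* In rheumatology-SD units it would be 79%, 67% and 47% at these ratios. With the root-mean-square of the two SDs as the unit it is about 88%, 86% and 84%. The protocol does not name the unit, so neither series is a property of the plan.

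The study is also declared exploratory, and Section 8.2 has SDs reported by subgroup, so unequal spread would be visible. Both facts lower the weight of the point. Neither corrects an interval.

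**Conclusion.** The point holds conditionally, as an inexpensive improvement rather than an error. At 400:400:200 a pooled-variance model gives 95% intervals that depend on equal SDs, which the protocol neither states nor supports. If the third group's SD is 1.25 to 2 times that of the others, coverage of its two contrasts falls to about 92% to 85%, and the rheumatology versus dermatology interval is 5% to 26% too wide. At a ratio of 1 there is no effect.

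These figures apply to the simple specialty model at the planned sizes. Multiple regression models were not examined. Group sizes for the intervals to first csDMARD or bDMARD will differ and cannot be derived from the protocol. The figures in Section 8.3 are not wrong.

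**What to change.** Add to Section 8.2: specialty contrasts for continuous endpoints analysed by linear models (time from symptom onset to diagnosis, and the continuous secondary scores) use heteroskedasticity-consistent standard errors, for example HC3, or Welch-type separate-variance contrasts. This protects coverage whichever group varies most. If the SAP already says so, a cross-reference is enough.

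Optionally, add to Section 8.3 that 0.281 assumes equal SDs, and that at an SD ratio of 1.5 the difference detectable with 90% power is about 0.38 rheumatology-SD units.

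The cost is one or two sentences and one line of analysis code. There is essentially no loss if the SDs are equal: in the simulation at a ratio of 1, separate-variance coverage was 94.9% to 95.1%. Sample size and data collection do not change.

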### 3. Introduction

Psoriatic arthritis (PsA) is a chronic systemic immune mediated inflammatory disease characterized by the association of arthritis and periarticular inflammation with skin psoriasis. PsA is regularly allied with plaque psoriasis and presents as asymmetric mono-/oligoarthritis or symmetric polyarthritis, distal interphalangeal (DIP) joint involvement and/or axial disease. Other common PsA features are enthesitis, dactylitis and psoriatic nail dystrophy (1-6).

PsA occurs in around 30% of patients with psoriasis, while its population prevalence estimates range from 0.1-0.5% worldwide (7, 8). Typically, psoriasis precedes the development of arthritic symptoms by several years (9, 10). However, the clinical patterns of PsA are heterogeneous and may vary in an individual patient over time, which renders recognition of the disease by non-rheumatologists and patients challenging (6, 11, 12).

The medical and economic burden of PsA could be significant for the patient and society. Up to 30% of PsA patients exhibit a progressive, disabling form of arthritis and almost 70% of PsA patients seen in clinics have evidence of erosive disease (2, 3, 11, 12). PsA may thus lead to impaired physical function, decreased quality of life, work disability, and is also associated with certain comorbidities.

Initially, the recognition of comorbidities has been limited to the classical features or extra-articular manifestations (EAMs) of spondyloarthritis, such as inflammatory bowel disease and uveitis (5, 11, 13-15). Over the past few years, it has been increasingly recognized that an increased prevalence of both novel and traditional cardiovascular risk factors as well as of established cardiovascular disease, such as ischaemic heart disease and cerebrovascular disease, represents a major source of morbidity and mortality in PsA (16-18). The burden of cardiovascular disease is larger in PsA than in psoriasis itself and may be reduced by systemic anti-inflammatory treatment (19, 20). Further, obesity, metabolic syndrome and type II diabetes mellitus, which occur frequently in PsA patients, may negatively affect disease activity and response to therapy (21-23). Of note, increased incidence rates of malignancies other than skin cancer, and similar to that in patients with rheumatoid arthritis, were found in the North American CORRONA database (24).

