## 4. Rationale

Evidence suggests that timely and effective management can improve long-term outcomes in patients with PsA. The factors influencing management decisions in PsA are not well understood. In the field of diabetes mellitus, the interactions of patient, physician and systemic factors were found to have implications for the implementation of a diabetes management model (39).

Early diagnosis of PsA is the first and crucial step in effective management of PsA, The detection of inflammatory musculoskeletal symptoms drives PsA diagnosis. The clinical patterns of PsA are heterogeneous and may vary in an individual patient over time, which renders recognition of the disease by non-rheumatologists and patients challenging, leading to a delay in diagnosis and worse long term outcomes. Therefore, the time of musculoskeletal symptoms onset is selected in this study as the anchor date for describing different management steps in patients with PsA. In order to assess this aspect in the overall PsA population both patients with established and suspected PsA diagnosis will be asked to participate in the study. Medical care of PsA patients are provided by various clinical specialties, such as rheumatologists, dermatologists, other specialists and primary care practices. In order to describe the overall PsA population, which includes patients with mild disease that are not consulting physicians with rheumatology or dermatology expertise, the study aims to include PsA patients from all specialties providing medical care.

This study is expected to provide important insights into the factors influencing management of PsA, which may aid planning improvements in the standards of care in this chronic systemic disease.

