### Secondary objectives:

- To explore the association between the timing of various management steps and current disease activity and burden in patients with a confirmed PsA diagnosis
- To describe the disease characteristics and comorbidities of patients whose suspected PsA diagnosis is not confirmed through a current routine rheumatological and dermatological assessment

This is an observational study. It is not designed to identify or quantify a safety hazard relating to an authorized medicinal product.

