## 7. Ethics and Quality

This observational study will be run in compliance with local laws and regulations. Notification/ submission to the responsible Ethics Committee, Health Institutions and/or Competent Authorities will be done as required by local laws and regulations.

Written patient authorization to use and/or disclose his/her anonymized health data (and informed consent where applicable) will be obtained prior to patient inclusion.

To maintain subject confidentiality, no demographic data that can identify the patient will be collected (e.g. initials, date of birth), only the patient age will be collected. In order to protect patient's identity, a unique number will be assigned to each patient and related study records.

Data Recording Forms (DRF) in English and patient questionnaires in local language will be provided to each site in paper format coded with a unique patient number. The participating site will be asked to send the filled out Forms/Questionnaires regularly to the AbbVie Affiliate office in the respective country (see section 11 Affiliate Agreement page).

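### Section 8.2 relates current activity and burden to the delay intervals without age or time since symptom onset, so the slopes can reflect longer disease or older age and not later management

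*Protocol*

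**What the plan says.** The first secondary objective (Protocol section 5) is "To explore the association between the timing of various management steps and current disease activity and burden in patients with a confirmed PsA diagnosis".

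For this objective the last paragraph of section 8.2 says: "Regression analyses will be done as described above, using time from symptom onset to PsA diagnosis". The explanatory variables that it fixes are, in full: "using time from symptom onset to PsA diagnosis, time from PsA diagnosis to first csDMARD, first bDMARD and from first csDMARD to first bDMAD". By pointing back to the preceding text it also takes over the modelling strategy given there, which is simple regressions for one variable at a time and then estimation "in multiple regression models with variable selection to identify and assess important explanatory variables". That preceding text names further explanatory variables for primary and secondary outcomes: "disease severity perception by patients and physicians and clinical specialty". Neither list contains age or time since symptom onset. Section 8.2 refers only the definition of the analysis populations to a separate statistical analysis plan.

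Three other places bear on the point. Section 4 makes symptom onset the anchor date and describes late recognition as "leading to a delay in diagnosis and worse long term outcomes". Section 3 says: "Up to 30% of PsA patients exhibit a progressive, disabling form of arthritis". Section 7 confirms that age is available: "only the patient age will be collected".

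**The concern.** Patients are assessed once, at differing times after onset. For each patient, time since onset equals the onset-to-diagnosis delay plus the time since diagnosis. Unless patients with long delays have correspondingly short times since diagnosis, delay and elapsed disease time are positively correlated. Age follows the same pattern more weakly.

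If a burden measure such as HAQ-DI worsens with disease duration or age, a regression on the delay picks up that worsening even when earlier diagnosis would have changed nothing. The planned variable selection does not help, because it cannot choose a variable that is not a candidate. Specialty and perceived severity do not stand in for duration.

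What is at stake is interpretation. Section 8.2 promises effect estimates with 95% confidence intervals. Against the background set out in section 4, a positive slope could easily be taken as support for earlier diagnosis or treatment.

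**Working it through.** **The plan's own figures.** The protocol gives no figure for these secondary regressions. It does give the sample size. At two-sided 5%, power is 89.9% for 400 vs 400 at effect size 0.229, and 90.0% for 400 vs 200 at 0.281, so the stated 90% reproduces. Recruitment of 400/0.90 + 400/0.85 + 200/0.75 = 445 + 471 + 267 = 1183 agrees with about 1200. The 1000 evaluable patients are used below.

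**Assumed inputs (none is in the protocol).** D is the delay, lognormal with mean 2 y (SD 3) or mean 3 y (SD 5). F is the time since diagnosis, exponential with mean 7 y (SD 7), independent of D. T = D + F is the time since onset. HAQ-DI = a + bT + error, with error SD 0.65 and b = 0.005, 0.01 or 0.02 per year. The true effect of timing is zero. Significant means that the 95% interval for the slope excludes zero.

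**Expected slope.** Given D, the mean of T is D + 7, so the regression of HAQ-DI on D alone has slope b. The whole yearly duration effect is attributed to delay.

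**Correlation of D with T.** SD(D)/√(SD(D)² + 7²) = 3/7.62 = 0.39, or 5/8.60 = 0.58 (0.57 in the simulated samples).

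**Rejection rate by formula.** For b = 0.01, SD(D) = 3, n = 1000:
- residual SD = √(0.65² + (0.01 × 7)²) = 0.654
- standard error = 0.654/(3 × √1000) = 0.0069
- z = 0.01/0.0069 = 1.45
- P(Z > 1.96 − 1.45) ≈ 0.31

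**Simulation, 1000 studies per cell, share significant:**

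| b per year | n=1000, delay SD 3 | n=1000, delay SD 5 | n=1000 with T added (SD 3 / SD 5) | n=300, SD 3 / SD 5 |
|---|---|---|---|---|
| 0.005 | 10.7% | 22.1% | 3.8% / 4.8% | 7.8% / 10.1% |
| 0.01 | 27.2% | 63.8% | 4.4% / 4.8% | 12.9% / 24.7% |
| 0.02 | 77.5% | 98.7% | 7.2% / 4.5% | 32.4% / 61.5% |

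Repeat runs put the lowest n=1000 cell at 10-13% and the highest at 99-100%. With b = 0 the unadjusted rate is 3.9-6.1%. The 300 is an assumed size for a treated subset.

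**Other assumed distributions, n = 1000, no delay effect.** Burden is correlated 0.1/0.2/0.3 with either T or age; age at onset has mean 40 and SD 12.

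| Setting | corr(D,T) | Burden driven by T | Burden driven by age |
|---|---|---|---|
| D and F independent, exponential, means 3 and 7 y | 0.39 | 25% / 71% / 96% | 11% / 27% / 51% |
| Onset uniform over 20 y, delay truncated at the visit | 0.23 | 11% / 30% / 56% | 4% / 9% / 14% |
| Delay unrelated to T and age | 0 | 5-6% | 3-6% |

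Adding T and age brings every cell to about 4-7%. Age alone is not enough: in the first setting, with burden driven by T, it leaves 16% / 47% / 79%.

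**The reverse case.** Suppose burden depends only on time since diagnosis, a + bF. Because F = T − D, the coefficient of D with T held fixed is −b. Under the first set of inputs the unadjusted slope then rejects in 4-6% of studies and the adjusted slope in 11-96% at n = 1000. The adjustment changes what the coefficient means.

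**Precision.** 1/√(1 − 0.39²) = 1.09 and 1/√(1 − 0.57²) = 1.22.

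**The case against.** The adjustment set of an exploratory regression is often left to the analysis plan, and 8.2 does not call its list exhaustive. This carries some weight. However, 8.2 names its explanatory variables itself and defers only the populations, so the point concerns what is stated. An analysis plan that is not shown here may already add the covariates.

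A reader might infer more than the documents support:

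- *That the intervals are the only variables.* They are not: multiple models are planned, and specialty and severity perception carry over. These do not remove duration.
- *That the analysis will reject whenever burden rises with duration or age.* The rate ranges from nominal to almost certain, depending on the correlations and on n, and the route through age alone is weak. Section 8.2 also sets no rejection rule; the 5% level appears only in 8.3, for the specialty comparisons.
- *That the objective cannot be answered, or that an error rate is broken.* The objective is an association and 8.3 calls the study non-confirmatory. A crude slope is an association. The rationale's remark on worse outcomes is background and does not define a causal estimand.

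Two further objections stand. Only one interval and one outcome were simulated, and a progressive form in up to 30% of patients does not show that current joint or skin activity rises with duration. The reverse case shows that holding time since onset fixed is a choice of estimand, so its meaning has to be stated.

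**Conclusion.** The concern holds in limited form. The variables named in 8.2 omit age and time since onset, so the interval slopes cannot separate late management from longer disease or older age. In the HAQ-DI simulations with no timing effect and 1000 patients, the unadjusted delay slope is significant in about 10% to 99% of studies for a rise of 0.005-0.02 units per year. It is significant in about 5% when burden depends on neither duration nor age. These rates rest on assumed distributions and on a delay that correlates positively with time since onset; without that correlation there is no inflation. This is a weakness in how an exploratory result can be read, worth correcting because the correction is cheap.

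**What to change.** In the last paragraph of 8.2, enter patient age and time from symptom onset to assessment as fixed covariates, outside the variable selection, in the regressions of activity and burden on each interval. Show the unadjusted slope as descriptive.

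State that the onset-to-diagnosis coefficient then compares patients whose symptoms began equally long ago, so that a longer delay also means a shorter time since diagnosis, and that the result remains an exploratory association. Delay, time since diagnosis and time since onset cannot all enter one linear model, because the first two sum to the third.

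No new data should be needed. Age is collected, and onset is the anchor date and is required for the first primary endpoint. The assessment date is assumed to be on the recording forms, which are not shown. The cost is a few sentences, two degrees of freedom, and a standard error for the delay slope roughly 10-20% larger under the assumed correlations, before any gain from a smaller residual variance.
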